### Data collection

Participants will serve as their own controls, with the primary outcome being the change in depression or anxiety status from baseline to exit after the 9 sessions. Assuming a 20% reduction in depression or anxiety (Cohen's d = 0.2), a sample size of 200 will provide 80% power. Data will be collected by the CHWs using secure tablets and the REDCap data collection platform will ensure real-time capturing, reporting and quality control (65). This study may provide early indications of the intervention's potential impact, helping to refine hypotheses for the efficacy trial. It will also evaluate whether the assessment measures are valid, reliable, and sensitive to this target population and context. Table 3 outlines the specific implementation data to be collected.

**Table 3 T3:** Implementation data collection.

Domain	Measure	Assessment time point		
		**Pre-assessment** (Before session 1)	**During intervention** (Session 1–Session 8)	**Post-assessment** (After session 8)
Demography	Sociodemographic questionnaire (date of birth; gender; language; relationship status; education; occupation; household assets; food insecurity)	✓	x	x
Medical	Medical questionnaire (prior diagnosis of anxiety, depression, tuberculosis, epilepsy, HIV; on medication for anxiety, depression, tuberculosis, epilepsy, HIV)	✓	x	✓
	WHO functional Impairments Questionnaire (36)	✓	x	x
	Blood pressure	✓	x	✓
Daily functioning	WHO disability assessment schedule 2.0 (71)	✓	x	✓
Tobacco, alcohol, and drug use	Tobacco use questionnaire (72); AUDIT-Questionnaire (73); drug use questionnaire	✓	x	✓
Stressful life events	Adverse childhood experiences questionnaire (74)	✓	x	✓
Anxiety	GAD-7 (30)	✓	x	✓
Depression	PHQ-9 (29)	✓	x	✓
Self-efficacy	Generalized self-efficacy scale (75)	✓	x	✓
Social support	Social support questionnaire	✓	x	✓
Sleep	Pittsburgh sleep quality index (76)	✓	x	✓
Psychological well-being	PSYCHLOPS (77)	✓	✓	✓
Suicide risk	WHO thoughts of suicide questionnaire (36)	✓	✓	✓

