**Methods:**

The prototype aims to implement a youth-centred community mental health intervention, through collaboration with existing public health systems and community resources. It seeks to enhance access to mental health support for adolescents and young people in Soweto, South Africa, by creating a dynamic and engaging therapeutic environment for those dealing with anxiety, depression, and suicidal ideation. This protocol outlines how we will evaluate the feasibility, acceptability, and implementation process of the prototype mental health intervention. We will enrol 200 at-risk adolescents and young people, aged 14–24 years, who will serve as their own controls, into the intervention and collect assessment and process evaluation data using mixed methods.

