## Introduction

We have the largest generation of young people in history, with 1.8 billion individuals aged 10–24 years, comprising 40% of the global population (1). Adolescence is a critical developmental period for physical growth and brain development (2), as well as the formation of social capital, defined as the support, trust, and resources available through interpersonal relationships and community networks (3). Mental disorders are increasingly prevalent among adolescents (4), with over 70% of mental disorders onset before age 25, and more than half of young people experiencing at least one episode of mental ill-health by this age (5). Additionally, up to one-third of suicide attempts occur among adolescents (6). Despite this, adequate management and treatment services are often lacking in public health systems to effectively address adolescent mental health needs (7, 8). In this context, community-based resources, such as peer networks, schools, and local organizations, can be sources of social capital, offering accessible and context-specific support for adolescents experiencing mental health challenges.

In Sub-Saharan Africa depression and anxiety are the most common mental health conditions, affecting 27% and 30% of adolescents, respectively (9). Young people in resource-constrained communities face increased risks due to poverty, exposure to trauma, and social dysfunction, evidenced by persistent difficulties in engaging with expected social roles and relationships, such as those with family, peers, or school (10–12). These challenges can inhibit service engagement (13–15), and stigma further prevents adolescents from seeking help, even in times of significant distress (16–19). Given that symptoms typically emerge around age 15 and mental health disorders show a median persistence rate of 80%, there is an urgent need for accessible, context-sensitive interventions (20, 21). In Sub-Saharan Africa, community-based interventions have the potential to reduce barriers to care, address stigma, and strengthen adolescent mental health support systems (22).

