### Study sample, recruitment, and eligibility criteria

We aim to enrol 200 adolescents (14–19 years) or young adults (20–24 years). Recruitment will be monitored closely, and where feasible, efforts will be made to maintain balance across age groups. However, achieving exact balance is not a formal requirement of the study design, and recruitment will proceed pragmatically within the target population. Participants will be recruited through established referral pathways from screening programs in Soweto that identify individuals at risk for depression, anxiety, or suicidal ideation using recognized screening tools: the Patient Health Questionnaire-9 (29), and Generalized Anxiety Disorder-7 (30) that are commonly used in this context (31). All referrals will be assessed by a social worker for eligibility. Eligible participants must: (i) reside in Soweto, (ii) be aged 14–24, (iii) score at risk for depression, anxiety, or suicidal thoughts on screening tools, and (iv) have a primary caregiver residing in the same household (for those under 18) who consents to their participation. Exclusions will apply to individuals with severe intellectual disabilities or communication difficulties, or those outside the age range. The inclusion and exclusion criteria can be found in Table 1 below.

**Table 1 T1:** Inclusion and exclusion criteria.

Category	Criteria	Description	Assessment method
Inclusion	Adolescents/youth aged 14–24 years	Defined age range of participants	Self-report with confirmation via ID, birth certificate, or caregiver report
	Living in Soweto	Residence within Soweto, Johannesburg	Self-report and/or local address verification
	Primary caregiver of adolescent is resident in the same household	Caregiver resides in same dwelling and has primary caregiving responsibilities	Self-report from both caregiver and adolescent
	Scored at risk of probable depression and/or anxiety and/or suicide ideation on screening tools	Positive screen on recognized screening tools	GAD-7 (30) score ≥10; PHQ-9 (29) score ≥10; The ‘at risk’ category reflects moderate symptoms reported in the past 2 weeks, consistent with prior studies using these tools to signal probable caseness (29–31)

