As a Phase I implementation study, we aim to monitor the impact of the B^3^ prototype rigorously and adaptively throughout its development and implementation. The combination of qualitative and quantitative evaluation methods will provide a comprehensive understanding of the intervention's effectiveness and feasibility. Additionally, this study will monitor the costs associated with the intervention, which is particularly important in resource-constrained settings. By collecting detailed cost data on design, implementation, and delivery, we aim to inform future assessments of economic feasibility and support decision-making regarding the potential for scale-up in similar contexts.

The findings from this study will play a crucial role in informing the development of a Phase II randomized controlled trial protocol aimed at assessing the efficacy, scalability, and sustainability of the B^3^ prototype. Insights gained from this Phase I implementation study can be used to refine the prototype based on participant feedback and data analysis, highlighting how specific components contribute to its overall effectiveness. This feasibility study will also identify potential risks and barriers, ensuring that the larger efficacy trial is both ethically and practically sound. By identifying practical and logistical challenges, such as staffing, technology access, and funding, early on, the study will help prevent costly mistakes in the full-scale trial and allow for more efficient planning. Demonstrating feasibility and acceptability increases the likelihood of securing funding approval and ethical clearance for the larger trial, offering evidence of the intervention's potential for success. Ultimately, fostering long-term resilience and well-being among adolescents and young people requires systemic changes in mental health care, with interventions like the B^3^ prototype leading the way toward more inclusive and responsive services in resource-constrained communities.

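### The powered primary outcome is an uncontrolled pre-post change in people selected for high scores, with baseline undefined; it cannot carry the Discussion's claims on effectiveness and component contributions

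*Protocol article*

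**What the plan says.** - **Entry.** Table 1 of the protocol article admits those who "Scored at risk of probable depression and/or anxiety and/or suicide ideation on screening tools", with the assessment method given as "GAD-7 (30) score ≥10; PHQ-9 (29) score ≥10". The same section says that participants arrive by referral from existing screening programmes that use these tools.
- **Control.** The abstract describes 200 participants "who will serve as their own controls, into the intervention", and Data collection repeats this: "Participants will serve as their own controls, with the primary outcome being the change in depression or anxiety status". No comparison group, run-in or repeated baseline is described.
- **Primary outcome and size.** Under Data collection it is "the primary outcome being the change in depression or anxiety status from baseline to exit after the 9 sessions". The sample of 200 is justified by 80% power for d = 0.2.
- **Measurement.** Table 3 schedules PHQ-9 and GAD-7 once before session 1 and once at the post-assessment. The text does not say whether baseline is that first score or the screening score, or whether a participant must still be above the cut-off at the first assessment.
- **Claims.** Data collection speaks of early indications of potential impact, and efficacy is left to a Phase II randomised trial. The Discussion, however, says that the combined methods "will provide a comprehensive understanding of the intervention's effectiveness and feasibility" and that the insights can be used to refine the prototype, "highlighting how specific components contribute to its overall effectiveness".

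**The concern.** People enrolled because a fluctuating score was high tend to score lower when measured again, and some recover without treatment. A comparison of each person with themselves, tested against zero change, counts both as improvement. The article mentions neither mechanism, although the sample is sized on this change and the Discussion attaches the word effectiveness to the evaluation.

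An unseen analysis plan would not remove the difficulty. The outcome, the own-control concept, the sizing and the interpretation are all stated here, and no analysis of these data can supply the missing untreated course.

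At stake is the Phase II decision. A significant improvement could be read as evidence of effect, and if its size were carried forward the randomised trial could be too small. The component claim has a related weakness: every participant rotates through all four stations, so the quantitative data contain no contrast between PM+, Brain Gym and VR.

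**Working it through.** **1. The plan's own figure.** Inputs from the article: d = 0.2, n = 200. Assumed: two-sided alpha 0.05, no dropout. Paired comparison: power = Φ(d√n − 1.96) = Φ(0.2 × 14.142 − 1.96) = Φ(0.868) = 80.7% (noncentral t: 80.4%). The stated 80% is reproduced, so the arithmetic is sound. The question is what a change from zero means.

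**2. Assumptions for regression to the mean.** The article gives no mean, SD or correlation. Assumed: normal scores, mean μ = 5 to 9, SD 5, cut at 9.5 (a whole-number score of at least 10), zero treatment effect, one scale. These means put 18% to 46% of the screened population above the cut; the Introduction's 27% and 30% lie inside that range. Write c = (9.5 − μ)/5, λ = φ(c)/(1 − Φ(c)), v = 1 + cλ − λ².

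**3. Baseline = screening score.** Fall = 5(1 − r)λ; SD of change = 5√[(1 − r)²v + 1 − r²].
- Example, μ = 7, r = 0.8: c = 0.5, λ = 1.141, v = 0.2685. Selected mean = 7 + 5 × 1.141 = 12.7. Fall = 5 × 0.2 × 1.141 = 1.14 points. SD of change = 5√(0.04 × 0.2685 + 0.36) = 3.04. Standardised change = 1.14/3.04 = 0.37; 29% are below 10 at retest.
- Over μ 5 to 9 and r 0.7 to 0.9: fall 0.43 to 2.17 points, standardised change 0.196 to 0.60, and 15% to 45% below 10. Eight of the nine combinations of μ = 5, 7, 9 and r = 0.7, 0.8, 0.9 exceed 0.2; the exception is μ = 9, r = 0.9.
- Chance of a significant improvement at n = 200 with an inert programme: Φ(0.196 × 14.142 − 1.96) = 79% at the lowest value, over 99% at 0.37.

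**4. Baseline = pre-session-1 score, no re-qualification.** With correlations screen-baseline r1, screen-exit r2 and baseline-exit r3, in SD units: mean change = (r1 − r2)λ; variance = 2(1 − r3) − (r1 − r2)²(1 − v).
- Equal correlations: the mean change is 0, because the regression has already happened by baseline.
- r1 = 0.8, r2 = 0.75, r3 = 0.8, μ = 9 (λ = 0.8626, v = 0.3422): 0.0431/√0.3984 = 0.07.
- r1 = 0.8, r2 = 0.70, r3 = 0.8, μ = 5 (λ = 1.4456, v = 0.2112): 0.1446/√0.3921 = 0.23.
- The chance of a significant improvement is 2.5% at zero change, and about 16% to 90% over 0.07 to 0.23.

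**5. Baseline = pre-session-1 score, participant must still be above the cut.** Numerical integration with r1 = r3 = 0.8, r2 = 0.70 to 0.80, μ = 5 to 9 gives 0.18 to 0.43. With all three correlations at 0.9, the lowest value is 0.12.

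**6. Natural remission, illustration only.** If a fraction f improves by k SDs of change and the rest do not change on average, d = fk/√[1 + f(1 − f)k²]. For k = 1 to 2: f = 5% gives 0.05 to 0.09, f = 10% gives 0.10 to 0.17, f = 20% gives 0.19 to 0.31. The article gives no remission rate over nine weeks, so f is an assumption.

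**The case against.** **The natural reading of baseline is Table 3's pre-session-1 score.** This stands, and it matters most. That score and the post-assessment are the only pair the study itself collects, and on that reading regression shrinks, possibly to nothing. The 0.20 to 0.60 range must therefore not be quoted without its condition. But the text fixes neither the baseline nor re-qualification, and remission remains on every reading.

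**A single arm is legitimate in Phase I, and the article hedges.** This also stands. The early-indications wording and the deferral of efficacy are appropriate. The effectiveness sentence in the Discussion goes further than that hedge.

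**Stronger readings that the documents do not support:**
- *A significant result is close to guaranteed with an inert programme.* This holds over most of the assumed range if baseline is the screening score, but not with a re-measured baseline and equal correlations.
- *Everyone starts positive, so six crossings out of 200 suffice.* Six one-way changes do give exact McNemar p = 2 × 0.5⁶ = 0.031. But this needs all 200 positive on a composite status at the screening measurement. Entry is either/or, so a participant can be below 10 on one scale. With a re-measured baseline some start below 10, and the protocol names no McNemar test.
- *The article's own persistence figure equals the planned effect.* The Introduction says that "mental health disorders show a median persistence rate of 80" percent, leaving 20%. No time frame is given, and non-persistence of disorders is not the same quantity as a 20% reduction equated with d = 0.2. The match is a coincidence.
- *Phase II will be underpowered.* A trial sized on d = 0.5 (64 per arm) has about 20% power if the true effect is 0.2, but nothing says the pre-post change will size Phase II.

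**The component quote has a context.** The sentence refers to participant feedback as well as data analysis, so a qualitative reading is partly there. The data-analysis half is what the design cannot deliver.

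**Conclusion.** The concern holds in conditional form and should be fixed. Remission, and regression to an extent set by the choice of baseline, can account for part or all of d = 0.2. The figures above rest on an assumed mean, SD, correlations and normality, on one scale at a time; either/or entry would dilute regression on a single scale. The conclusion does not depend on the exact values: without a comparison the change cannot be attributed to the programme, and without variation in components it cannot be divided among them. The study's feasibility and acceptability aims are unaffected.

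**What to change.** 1. Under Data collection, define baseline as the pre-session-1 PHQ-9 and GAD-7 in Table 3, not the screening score.
2. State that the pre-post change is descriptive and reported with a confidence interval, that regression to the mean and natural remission prevent its being evidence of effect, and that it will not be the Phase II effect size. Carry forward the SD, the pre/post correlation and retention instead.
3. In the Discussion, replace the effectiveness claim with feasibility, acceptability and early indications, and limit component contributions to participants' qualitative perceptions.
4. Optionally, where dated referral scores can be obtained, report the screening-to-pre-session change as context. It is not a like-for-like control, since that interval absorbs most of the regression, and it should not be subtracted from the pre-to-exit change.

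Items 1 to 3 are wording only. Item 4 depends on the screening programmes supplying individual scores and dates. The price is a weaker claim in the results paper.

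### The 80% power statement merges a status outcome, a 20% reduction and Cohen's d = 0.2; it fits only a paired test on a continuous score and is not a power statement for the status outcome

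*Protocol article*

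**What the plan says.** The Data collection section of the protocol article makes each participant their own control, with "the primary outcome being the change in depression or anxiety status from baseline to exit". The next sentence gives the only sample-size justification in the document: "Assuming a 20% reduction in depression or anxiety (Cohen's d = 0.2), a sample size of 200 will provide 80% power".

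The section does not say how status is derived. The only definition of being at risk is in Table 1, under the eligibility criteria, where the thresholds are "GAD-7 (30) score ≥10; PHQ-9 (29) score ≥10". Entry requires a positive screen: "Scored at risk of probable depression and/or anxiety and/or suicide ideation on screening tools". Table 3 lists PHQ-9 and GAD-7 both before session 1 and at the post-assessment, so continuous scores exist at both time points.

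**The concern.** The two consecutive sentences use three effect scales as if they were one.

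- **Status** is most naturally yes/no, at risk or not. Power for a paired yes/no outcome depends on the share at risk at baseline and on how many people cross the threshold in each direction.
- **A 20% reduction** is a relative (or possibly absolute) change in a proportion, or a relative change in a mean score.
- **Cohen's d = 0.2** is a mean change in SD units on a continuous score.

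If they do not coincide, the 80% describes an analysis other than the primary one. That affects how a null or positive result is read here. It also matters later: the article says the study will refine hypotheses for, and inform, a Phase II randomised trial. Someone who carries forward 20% and someone who carries forward d = 0.2 would size that trial very differently.

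**Working it through.** **Inputs from the article:** 200 enrolled, one group, paired comparison; effect given as 20% and as d = 0.2; power 80%; cut-offs of 10. **Not stated, so assumed:** two-sided 5%; means, SDs, pre-to-exit correlation, baseline share at risk and crossing rates, all shown as ranges.

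**1. The plan's own figure.** Paired t-test with d = mean change / SD of change and noncentrality d√n. At n = 200 the noncentrality is 0.2 × √200 = 2.83, and power is 80.4%. At n = 199 it is 80.2%; at 198 it is just under 80%. So N = 200 and 80% reproduce for a continuous paired change. This needs d on the SD of the change. If d is on the baseline SD, the paired effect is 0.2/√(2(1−r)), and power is 60.5%, 80.4% or 95.3% for a correlation r of 0.2, 0.5 or 0.7.

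**2. Is a 20% fall in mean score d = 0.2?** d = 0.2 × mean / SD, so the two coincide only if the SD equals the mean.
- Mean 12, SD 5: 0.2 × 12/5 = 0.48. Mean 15, SD 3: 0.2 × 15/3 = 1.0.
- Conversely, d = 0.2 is a relative fall of 0.2 × SD / mean: 0.2 × 3/15 = 4% to 0.2 × 5/12 = 8%.

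**3. Power for a yes/no status, n = 200.** Exact McNemar test, two-sided 5%. Let p10 be the proportion at risk at baseline but not at exit, and p01 the reverse. The number of discordant pairs M is Binomial(200, p10 + p01). Given M, the downward moves are Binomial(M, p10/(p10 + p01)), tested against one half. In the rows marked φ, p11 = p0·p1 + φ√(p0(1−p0)p1(1−p1)), p10 = p0 − p11 and p01 = p1 − p11, where p0 and p1 are the shares at risk at baseline and exit.

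| Assumed scenario | p10 | p01 | Power |
|---|---|---|---|
| 20% relative fall, 100% to 80% | 0.200 | 0 | >99.9% |
| 20% relative fall, 70% to 56%, φ = 0.5 | 0.194 | 0.054 | 98.1% |
| same, φ = 0 | 0.308 | 0.168 | 80.0% |
| 20% relative fall, 50% to 40%, φ = 0.5 | 0.178 | 0.078 | 77.8% |
| same, φ = 0 | 0.300 | 0.200 | 47.9% |
| d = 0.2 shift, mean 11 (59% to 51% at risk) | 0.208 | 0.128 | 44.5% |
| d = 0.2 shift, mean 14 (81% to 75% at risk) | 0.150 | 0.091 | 34.3% |
| d = 0.2 shift, mean 11, baseline limited to scores ≥10 | 0.353 | 0 | >99.9% |
| d = 0.2 shift, mean 14, baseline limited to scores ≥10 | 0.184 | 0 | >99.9% |

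The d = 0.2 rows assume normal scores with SD 4.5 and correlation 0.5, so the SD of the change is 4.5 × √(2 × 0.5) = 4.5 and the shift is 0.2 × 4.5 = 0.9 points. Placing the cut at 9.5, to allow for whole-number scores, moves the unrestricted range to about 31% to 44%.

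The last two rows are high largely because of regression to the mean: when everyone starts above the cut, people can only cross downward. They show how far the answer depends on what serves as baseline, not that the study can detect an intervention effect.

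**The case against.** The strongest reply is that no calculation is wrong: 80% at N = 200 reproduces for a paired continuous change of d = 0.2. That stands.

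Second, status is not explicitly defined as binary for the primary outcome. The cut-offs of 10 are eligibility criteria, and an article may leave the derivation and the test to a fuller document. This also stands, and it is why yes/no is called here the most natural reading rather than the declared one. It does not remove the problem. The point rests on a printed equation of 20% with d = 0.2, next to an outcome worded as status, and no later document can make those quantities equal.

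Third, a reader might infer that the primary comparison is underpowered, citing the 31% to 45% range. The document does not support that. Those figures come from unselected scores with only about 59% to 81% at risk at baseline, whereas entry requires a positive screen. With the same scores restricted to 10 or more at baseline, the test rejects almost always. The article does not say whether the screening score serves as baseline. If the 20% is read as a fall in a combined depression-or-anxiety status that nearly everyone has at entry, power is far above 80%. Shortfalls arise mainly for a single condition with roughly half or fewer positive at baseline, or for a small score shift that is dichotomised; neither is stated.

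Fourth, some status scenarios do give about 80%, such as 70% to 56% with φ = 0. That does not rescue the sentence, because it needs a baseline share and crossing rates that the article does not give, and d = 0.2 plays no part in it.

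Finally, this is a single-arm Phase I feasibility and acceptability study, with efficacy left to a later randomised trial. That limits the consequences, but the power figure is still attached to a named primary outcome.

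**Conclusion.** The concern holds as a mismatch between outcome and effect size, not as a demonstrated loss of power. The stated 80% is a power statement for a paired continuous change of 0.2 SD of the change (199 pairs for 80%, 80.4% at 200, two-sided 5% assumed). It is not one for a status outcome. Power for status is undetermined from the document: it runs from about one third to almost 100% across the assumed scenarios, on both sides of 80%. Nor is a 20% fall in mean score equal to d = 0.2; it is d = 0.48 to 1.0 for assumed means of 12 to 15 and SDs of 3 to 5.

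The mismatch itself needs no assumption beyond the two sentences. Its size depends on the assumed means, SDs, correlation and baseline shares, and the status figures also on reading status as yes/no at a cut of 10.

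**What to change.** Reconcile the outcome and the effect size in the Data collection section, in one of two ways.

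- **Score as primary.** Define the primary outcome as the change in continuous PHQ-9 and/or GAD-7 score from before session 1 to exit, and make change in status secondary. Delete the 20% reduction. State the power as: *199 complete pairs give 80% power for a mean change of 0.2 SD of the change, two-sided 5%.*
- **Status as primary.** Define status and its baseline measurement, and replace the sentence with a McNemar calculation that states the assumed baseline share at risk and the proportions crossing the threshold in each direction.

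Either resolves the point. The first needs no new assumptions. Under both, the cost is wording only, since both scores are already collected before and after. The downside of the first is that a mean score change is less intuitive than a change in status, which is why status should stay as a secondary outcome.

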### Process evaluation

Following MRC guidance on process evaluation (61, 62), we will assess implementation feasibility, mechanisms of impact, and context. Implementation feasibility assessment will focus on what is delivered and how, with compliance monitored via logs and discussions, to determine whether recruitment, retention, and implementation strategies are effective in this setting. Fidelity will be evaluated through observations of CHWs during one-on-one sessions by the social worker, while intervention dose will be tracked using diaries to record contact frequency and duration. Process indicators, including recruitment and retention, and indicators of program delivery will also be assessed. To understand the intervention's impact and how it meets the mental health needs of adolescents and young people, the acceptability of the intervention will be explored by focusing on the participants’ experiences. In-depth interviews and focus groups will be conducted with participants, caregivers, and the CHWs delivering the intervention, asking questions based on the seven component constructs of acceptability (66), as detailed in Figure 5 below. In assessing the context, we will aim to identify factors that might act as barriers or facilitators to intervention implementation or effects. These qualitative methods (interviews and focus groups) will be used to further explore specific issues of relevance, in terms of participants’ experiences of B^3^, key issues facing participants and factors influencing implementation.

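### The 80% power claim uses the full 200 to be enrolled as complete pairs, leaving almost no room for loss, and no exit score is scheduled for participants who stop early

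*Protocol article*

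**What the plan says.** The section on study sample, recruitment and eligibility sets the enrolment target: "We aim to enrol 200 adolescents" or young adults.

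The Data collection section gives the design ("Participants will serve as their own controls") and the primary outcome: "the change in depression or anxiety status from baseline to exit after the 9 sessions". The sample size rests on one sentence. It begins "Assuming a 20% reduction in depression or anxiety (Cohen's d = 0.2") and concludes that "a sample size of 200 will provide 80% power". It gives no alpha, no sidedness, no standardiser for d and no allowance for loss.

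Table 3 in the same section marks PHQ-9 and GAD-7 before session 1 and at the post-assessment, and not during the intervention. PSYCHLOPS and the suicide-risk questionnaire are the only measures taken at all three time points.

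The Process evaluation section lists retention among the things to be learned: compliance is monitored "to determine whether recruitment, retention, and implementation strategies are effective in this setting".

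**The concern.** The number to be enrolled and the number behind the power statement are the same. A paired analysis counts only participants with both a baseline and an exit score, so the 80% holds only if nearly all of those enrolled supply both. The programme asks for weekly attendance over 9 weeks, and the protocol does not take retention for granted.

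The second part concerns when the outcome is measured. Exit is defined by the end of the sessions, and the two instruments behind the primary outcome have no other post-baseline time point. As scheduled, a participant who stops early has a baseline score and no set second score.

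Two things are at stake. The published power may not describe the data that the study obtains. The change estimate, which the protocol hopes will give an early signal of impact and help shape the later efficacy trial, may also rest mainly on those who finished. With a single group, there is no comparison arm in which selective loss would show.

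**Working it through.** **Inputs from the protocol.** Single group, each participant their own control; d = 0.2; N = 200; power 80% (all Data collection). Enrolment 200 (Study sample section). No loss rate is given.

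**Assumptions.** Two-sided alpha of 5%; d is the mean change divided by the SD of the change; a paired t-test; loss rates of 5% to 30%.

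**Step 1: reproduce the stated figure.**

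- Normal approximation: n = ((1.960 + 0.842) / 0.2)² ≈ 196.2, rounded up to 197.
- Noncentral t with noncentrality 0.2 × √n and n − 1 degrees of freedom: power is 79.97% at 198, 80.2% at 199 and 80.4% at 200. So 199 pairs are needed.

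The stated 80% at 200 is reproduced. Two other readings do not fit. One-sided 5% gives 88.0% at 200 and needs only 155 to 156 pairs. Two independent groups of 100 give 29%.

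**Step 2: room for loss.** 200 − 199 = 1 participant (200 − 197 = 3 by the normal approximation).

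**Step 3: power if exit scores are lost** (same test, d = 0.2).

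| Assumed loss | Complete pairs | Power | Detectable d at 80% power |
|---|---|---|---|
| 0% | 200 | 80.4% | 0.199 |
| 5% | 190 | 78.3% | not computed |
| 10% | 180 | 76.1% | 0.210 |
| 20% | 160 | 71.0% | 0.223 |
| 30% | 140 | 65.2% | 0.238 |

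**Step 4: sensitivity to the standardiser.** If d is the mean change divided by the raw SD of the score, the effect on the change scale is 0.2 / √(2(1 − ρ)), where ρ is the pre-post correlation. The document gives no ρ, so a range is shown.

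| ρ (assumed) | Effect on change scale | Power, 200 pairs | Power, 160 pairs | Power, 140 pairs |
|---|---|---|---|---|
| 0.3 | 0.169 | 66% | 57% | 51% |
| 0.5 | 0.200 | 80% | 71% | 65% |
| 0.7 | 0.258 | 95% | 90% | 86% |

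At ρ = 0.5 the two readings coincide. At 0.7 a 30% loss is easily absorbed. At 0.3 the claim fails even with no loss.

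**Step 5: the measurement schedule.** The primary outcome needs PHQ-9 or GAD-7 at baseline and at exit. Table 3 takes them before session 1 and once more after the last session. No occasion is set for someone who leaves between those points. The article neither provides for an exit assessment of early leavers nor rules one out.

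**The case against.** The strongest reply has four parts.

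First, a reader might infer that the primary result will be a completers-only analysis. The document does not say so. It names no analysis set for the primary outcome, and the exit time points can be read as labels for the planned course. An exit assessment for early leavers, a missing-data method and the analysis population could all stand in a full protocol or analysis plan. This stands, and it limits the point to a risk created by the schedule as published. What remains is that an analysis plan can choose how to handle missing scores but cannot supply scores that were never collected. The assessment schedule is fixed in this document.

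Second, a reader might infer that the stated power fails at any realistic retention. That is not established either. Alpha and standardiser are unstated, and under the raw-SD reading with a high correlation the power survives considerable loss. The outcome is also described as a status, which may not be a continuous score at all. What stands is that the one simple reading that reproduces the 80% leaves almost no reserve.

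Third, one might suppose that those who stay are those improving, so that the change is overstated. Young people who feel better may also leave. Because entry requires a raised screening score, leavers' scores may also fall through regression to the mean. The documents give no figure from which to set a direction or size, and any worked example would rest on invented inputs.

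Fourth, this is a Phase I feasibility study with efficacy deferred to a randomised trial, and the loss of power is gradual. At 10% loss the detectable d moves only from about 0.20 to 0.21. This is fair, and it is why the point is not rated higher.

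**Conclusion.** The point holds at moderate severity. The power statement is arithmetically right for about 200 complete pairs, but the same 200 is the enrolment target, in a study that sets out to learn what retention will be. Under a paired test with d standardised by the SD of the change and two-sided 5% alpha, power falls to between 78% and 65% as loss runs from 5% to 30%. These loss rates are assumed. Under a raw-SD reading the result can be better or worse, depending on a correlation that the document does not give, so alpha and standardiser need to be stated before the 80% can be interpreted.

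On measurement, the schedule sets no exit PHQ-9 or GAD-7 for participants who stop early, which risks a change estimate drawn mainly from completers. Whether that would raise or lower the estimate, and by how much, is unknown.

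**What to change.** 1. Keep 200. State the alpha, its sidedness and the standardiser of d, and restate the power for the expected number of complete pairs. Under the reading used here, examples are 76% for d = 0.2 (or 80% for d of about 0.21) at 10% loss, and 71% (or 80% for d of about 0.22) at 20% loss. Holding 199 pairs at 20% loss would instead need 199 / 0.8 = 248.75, so 249 enrolled. For a feasibility study, restating the claim is the lighter remedy.
2. Schedule the exit PHQ-9 and GAD-7 in a fixed window around the planned end of the programme for every enrolled participant, whatever number of sessions they attended. For those who attend on schedule, this should be close to the assessment already planned. The primary outcome places exit after nine sessions and Table 3 places it after the eighth. The two must be reconciled before the window is set.
3. Report the change for all enrolled, with completers as a secondary result.

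The cost is a less favourable stated power and some follow-up contact with early leavers by existing staff. The community health workers already collect these data on tablets. No added enrolment and no new instrument is needed.
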